#### Primary outcomes

*Psychological flexibility* will be measured with the Acceptance and Fusion Questionnaire for Youth (AFQ-Y) [68, 69] at T0, T2, T4 and T5. The AFQ-Y contains 17 items that are rated on a 5-point Likert scale ranging from 0 = “*not at all true*” to 4 = “*very true*”. The psychometric properties of the AFQ-Y are demonstrated both in adolescent and adult samples [68, 70]. During T1 and T3, a short version (8 items) of the AFQ-Y will be administered (i.e., the AFQ-Y-8), which also has adequate psychometric properties [68, 69].

The *number of DSM-5 diagnoses* will be measured with the Structured Clinical Interview for DSM-5 Disorders—Junior (SCID-5-Junior) [71] at T0, T4 and T5. The SCID-5-Junior is a semi-structured diagnostic interview that assesses a wide range of DSM-5 disorders in children and adolescents. Preliminary results of studies investigating the psychometric properties of the SCID-5 junior show adequate parent–child agreements (except for externalising problems and insomnia) and an adequate convergent validity (especially in clinical samples) [71]. The SCID-5-junior will be conducted by trained research assistants working at the participating institutions. All research assistants will video/audio tape two SCID-5-junior interviews. The recorded SCID-5-junior interviews will be rated by an independent researcher to calculate the inter-rater reliability.

#### Secondary outcomes

The *presence of the primary DSM-5 diagnosis* will also be measured with the SCID-5-Junior [71] at T0, T4 and T5.

*Psychopathology* will be assessed by means of two informants: TAY will fill out the Youth Self Report (YSR) [72] at T0, T4 and T5 and parents/caregivers will fill out the Child Behavior Checklist about their child (CBCL) [73] at T0, T4 and T5. Some questions are slightly adjusted to make them more developmentally sensitive for young adults above the age of 18 (e.g., “*I cut classes or skip school*” will be adjusted to “*I cut classes or skip school/work*”). The YSR contains 69 items and the CBCL contains 74 items that are rated on a 3-point Likert scale ranging from 0 = “*not true*” to 2 = “*very true or often true*”. The psychometric properties of the YSR and CBCL are adequate [72, 73].

A short questionnaire measuring psychopathology, which is based on the YSR, the Behavior and Feeling Survey (BFS) [74], will be administered during all six assessments to register changes in psychopathology during the intervention. The BFS contains 12 items that are rated on a 5-point Likert scale ranging from 0 = “*not*” to 4 = “*always*”. The psychometric properties of the BFS are adequate [74].

The Severity Indices of Personality Problems – short form (SIPP-SF) will be used to measure *personality problems* (i.e., degree of self-control, identity integration, responsibility, relational capacities and social concordance) at T0, T2, T4 and T5 (derived from the SIPP–118) [75]. The SIPP-SF contains 60 questions that are rated on a 4-point Likert scale ranging from 0 = “*fully disagree*” to 3 = “*fully agree*”. The psychometric properties of de SIPP-SF are adequate [76].

*Global functioning* will be rated by two informants. Therapists will rate the global functioning of the TAY on the Children Global Assessment Scale (CGAS) [77, 78] at T0, T2, T4 and T5. TAY will rate their own global functioning by means of the Outcome Rating Scale (ORS) [79] at all six assessments. The CGAS is a numeric scale from 1 = “*needs constant supervision*” to 100 = “*superior functioning in all areas*” that is used by mental health care workers to rate the general functioning of youth. The description of the scale has been slightly adjusted to make it more developmentally sensitive for young adults above the age of 18 (e.g., “*no problems at school*” will be adjusted into “*no problems at school/work*”). The CGAS was found to be reliable between raters and across time. Moreover, it demonstrated both discriminant and concurrent validity [78]. The ORS consists of four numeric scales ranging from 1 to 10 in which TAY rate how well they have been doing in four life areas (i.e., individually, interpersonally, socially and overall). The ORS represents a balanced trade-off between the reliability and validity of longer measures [79]. Moreover, the ORS has a moderately high to high internal consistency and can be used as a screening measure and monitoring tool for subjective symptoms of psychological distress [80].

For this study we developed the Individual and Societal Impact Questionnaire (ISIQ) [81] to measure the TAY’s *individual and societal functioning* at T0, T4 and T5. The questionnaire contains 10 questions about the following areas: physical health, mental health, personal hygiene, school and work, friendships, romantic relationships, family, daily activities, independence and leisure time. For each area the following question will be asked: “*Within the last two weeks, how much difficulty did you have with..”.* All questions are answered on a 6-point Likert scale ranging from 0 = “*none*” to 5 = “*a lot*”.

To measure *quality of life* as expressed in quality adjusted life years (QALYs), the Dutch version of the EuroQol 5 Dimension Questionnaire (EQ-5D adolescent and parent version) [82] will be administered at T0, T2 (only for TAY), T4 and T5. The EQ-5D assesses five dimensions: mobility, self-care, usual activities, pain/discomfort and anxiety/depression. Participants are asked to indicate whether they/their children experience “*none”*, “*a little”*, or “*a lot” *of problems in the aforementioned domains. Furthermore, participants are asked to rate their/their child’s health on a scale ranging from 1 = “*the worst imaginable health state*” to 100 = “*the best imaginable health state*”. The psychometric properties of both the TAY and parent version have been established in earlier research [83, 84].

*Stress* will be measured using the Perceived Stress Scale (PSS-10) [85, 86] at T0, T2, T4 and T5. The PSS contains 10 questions that are rated on a 5-point Likert scale ranging from 0 = “*never*” to 4 = “*very often*”. The psychometric properties of the PSS are acceptable [87]. At T1 and T3 a short version of the PSS will be used, the PSS-4 [85]. Also the PSS-4 was found to have acceptable psychometric properties [85, 88]. Based on factor analysis we added one extra question (i.e., the question with the highest factor loading) to the PSS-4.

*Treatment Satisfaction* will be assessed with the Service Satisfaction Scale (SSS) [89] at T5. The SSS contains 4 items that are rated on a 4-point Likert scale ranging from 0 = “*disagree*” to 3 = “*agree*”. The psychometric properties of the SSS are considered as good [89].

Information about *drop-outs* will be gathered with a short drop-out questionnaire containing 5 questions (i.e., reason for drop-out, date of drop out, number of sessions followed, person who initiated to stop the treatment) reported by the therapist.

The quality of the *therapeutic alliance* will be measured with the Therapy Alliance Scale for Adolescents (TASC) [90] at T1, T2, T3 and T4. Both the TAY and the therapist are used as informants. The TASC contains 12 questions that are rated on a 4-point Likert scale ranging from 0 = “*this doesn’t suit me*” to 3 = “*this suits me very well*”. The internal consistency of the TASC has been qualified as good [91].

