#### Sample size calculation

We calculated the sample size for a two-level multilevel analysis, using the Optimal Design program [64]. In accordance with our planned analyses, the first level represents the TAY and the second level represents the therapists. As most of the therapists either give the ACT your way or the TAU intervention, we calculated the sample size as for a cluster RCT in which the therapists represent the clusters. Within our sample size calculation, we used a cluster size (i.e., the expected number of therapists) of 70, as we expect that in both conditions approximately 35 therapists will be carrying out either the ACT your way or TAU intervention. In addition, we used an ICC of 0.05 as this is the average ICC reported in meta-analyses of therapist effects in psychological intervention research [65]. Furthermore, the effect size is based on a meta-analysis in which 39 RCT’s were included that investigated the efficacy of ACT, including 1,821 adults with various mental disorders [21]. We based the effect-size on this meta-analysis as, to our knowledge, this is the most recent meta-analysis examining the effects of ACT transdiagnostically. When ACT was compared to TAU a medium effect was found (Hedges g = 0.64), when ACT was compared to CBT a small effect was found (Hedges g = 0.32). In this study ACT will be compared to TAU, presuming a medium effect around 0.64. However, since we want to be conservative and expect that, at least with some of the participants, CBT will be used in TAU as well, an effect size of 0.50 was included in the sample size calculation. Hence, with a cluster size of 70, an effect size of 0.50, an ICC of 0.05, an α of 0.05 and a power of 0.8, a sample size of 140 (i.e., on average two TAY per therapist, and 70 TAY per condition) is assumed.

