### Study design and procedure

The study is designed as a multi-center, randomized controlled trial (RCT). Data will be collected in 14 Dutch and Belgian mental healthcare institutions. Within each institution, TAY meeting the inclusion/exclusion criteria, their parents/caregivers and their therapists will be asked to participate in the study. Parents/caregivers of adolescents younger than 16 will be directly involved in the study. TAY aged 16 and older will be asked first for permission to contact their parents/caregivers. If they agree, their parents/caregivers will be asked to participate in the study as well. Before enrolling in the study, written informed consent from TAY and parents/caregivers/legal representatives (for adolescents younger than 16) will be obtained. If parents/caregivers and therapists agree to participate, they will be asked for their own written informed consent as well.

In total, six multiple informant (TAY, parents/caregivers, therapist) assessments will be conducted: at baseline (T0), after 3 sessions (T1), after 6 sessions (T2), after 9 sessions (T3), at post-intervention (T4) and at 6-month follow-up (T5). Assessments will include diagnostic interviews (at T0, T4 and T5) and questionnaires (at T0 to T5). The assessments will be conducted by research assistants working at the participating institutions (e.g., master students and psychologists). Research assistants will be trained in administering the diagnostic interview and questionnaires. The TAY will receive a 30 euro gift card as a reward (5 euros per assessment). After the baseline assessment (T0), TAY will be randomly assigned to either the ACT your way or TAU condition using a computer generated block design. At each institution, five participants will be randomly allocated to the ACT your way condition and five participants will be randomly allocated to the TAU condition (blocksize = 10). See Fig. 1 for an overview of the study design.

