### Study conditions

#### ACT your way

ACT your way consists of 12 weekly sessions, that can be carried out both individually as in groups. The therapists at the clinical institutions decide if they carry out ACT your way individually or in a group. There is a guide for therapists [66], a workbook for TAY [67] and a website with additional videos, mindfulness exercises and information for TAY. Each session lasts either 120 (group therapy) or 60 (individual therapy) minutes and has a fixed format in which psychoeducation, mindfulness exercises, metaphors and experiential exercises are carried out. The 12 sessions are divided into four blocks, each comprising of three sessions. The first block focusses on values (i.e., desires regarding development, identity, and autonomy). The second block focusses on the six core processes of psychological inflexibility (i.e., experiential avoidance, cognitive fusion, dominance of conceptualized past and feared future, attached to the conceptualised self, lack of values, and inaction). The third block focuses on acquiring skills based on the six core processes of psychological flexibility (i.e., acceptance, cognitive defusion, contact with the present moment, self as context, values, and committed action). With these skills, TAY can consciously choose behaviours that fit their chosen values. The fourth block focusses on continuing and strengthening TAY’s psychological flexibility and preparing the TAY for possible relapses in the future. In this study, ACT your way will be carried out in a face-to-face format by therapists working at the participating mental healthcare institutions. The therapists will be trained in using ACT your way (i.e., a two day training in the basics of ACT and a two day training in ACT your way specifically). Moreover, during the course of the study, the therapists will be supervised by an ACT expert.

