#### Effectiveness

The effect of the intervention on the primary (i.e., psychological flexibility and number of DSM-5 diagnoses) and secondary outcomes (i.e., presence of the primary DSM-5 diagnosis, psychopathology, personality problems, global functioning, individual and societal functioning, quality of life, stress, treatment satisfaction, drop-out and therapeutic alliance) will be evaluated using a two-level multilevel analysis in Mplus [115]. Specifically, we will investigate, if condition (i.e., ACT or TAU) predicts the post-intervention (T4) and 6-month follow-up (T5) levels of our primary and secondary outcomes, while controlling for the baseline levels of the concerning outcomes. We will perform a two-level multilevel analysis as we expect that TAY will be nested within therapists. Hence, the first level will represent the TAY and the second level will represent the therapists. We do not expect variance at the measurement level, as the analyses will be performed separately for the post-intervention and 6-month follow-up assessments. Although we expect that therapists will be nested within institutions, we will not include a third level as the number of institutions in our study is too small (i.e., 14 institutions). Instead, in all analyses, we will add dummies representing the mental healthcare institutions.

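### The CGAS comparison rests on therapists who know the treatment they give and mostly work in one arm, so any arm-wide difference in rating is confounded with condition.

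*Protocol article*

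**What the plan says.** All references are to the protocol article.

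- **Rater.** Secondary outcomes: "Therapists will rate the global functioning of the TAY on the Children Global Assessment Scale (CGAS". Table 1 likewise gives the therapist as the only source for this instrument. No masked or independent CGAS rater is described.
- **Which therapists.** Study design and procedure says of eligible youths that "their parents/caregivers and their therapists will be asked to participate in the study". The ACT your way section adds that "ACT your way will be carried out in a face-to-face format by therapists working at the participating mental healthcare institutions".
- **Order of events.** "After the baseline assessment (T0), TAY will be randomly assigned to either the ACT your way or TAU condition" (Study design and procedure).
- **Therapist and arm.** Sample size calculation: "most of the therapists either give the ACT your way or the TAU intervention", with about 35 therapists expected per condition.
- **Analysis.** Effectiveness: T4 and T5 outcomes are regressed on condition "while controlling for the baseline levels of the concerning outcomes", with therapists as the second level and dummies for the 14 institutions.
- **Other assessments.** "The assessments will be conducted by research assistants working at the participating institutions". Assistants are trained to give the diagnostic interview, which takes place at T0, T4 and T5.
- **Timing of the CGAS.** The Secondary outcomes text lists T0, T2, T4 and T5. Table 1 marks T0, T2 and T4 only.

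**The concern.** Most outcomes in Table 1 are self-reports, parent reports or results of an interview by an assistant. The CGAS is the only functioning or symptom outcome that the therapist scores. The Discussion presents the use of several informants, therapists among them, as a strength.

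A therapist who scores the CGAS at T4 is, on the natural reading, judging the result of their own work and knows which treatment was given. Because therapists are largely nested within arm, the ACT scores come mainly from one group of raters and the TAU scores from another. If the two groups differ on average in how generously they rate, that difference appears as a treatment effect. ACT therapists receive two two-day trainings and expert supervision in the treatment whose result they then rate, so equal rating behaviour cannot be taken for granted.

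A second, lesser issue is that allocation follows T0. The treating therapist is therefore generally not settled when the baseline CGAS is scored, and baseline and outcome will often come from different raters.

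**Working it through.** **The plan's own figure.** The documents give no figure for the CGAS. The planning effect of 0.50 serves below as a yardstick, so its calculation was checked first. Inputs from Sample size calculation: J = 70 therapists, n = 2 youths each, d = 0.50, ICC = 0.05, α = 0.05 (taken as two-sided). The non-centrality is λ = J·d² / (4·(ICC + (1 − ICC)/n)) = 70 × 0.25 / (4 × 0.525) = 17.5 / 2.1 = 8.33. With 1 and 68 degrees of freedom the power is 0.812, so 140 reproduces. Nothing in this point changes it.

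**What the model can and cannot remove.** For youth i of therapist j, write the T4 score as

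Y = μ + τ·A + δ·A + β·Y0 + institution + u_j + e,

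where A is condition, τ the true effect, δ an arm-wide difference in rating, Y0 the T0 score and u_j the therapist effect. The coefficient of A estimates τ + δ. Each planned term in turn:

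1. *Therapist random effect.* u_j has mean zero over therapists. It takes up differences between therapists within an arm, but not a shift shared by an arm.
2. *Institution dummies.* Each institution allocates five youths to each arm, so δ operates within institutions and the dummies leave it in place.
3. *Baseline CGAS.* T0 is scored before allocation, so Y0 carries no arm-wide shift that could offset δ. Baseline adjustment could offset part of a stable leniency difference only if the later therapist had also scored T0, which the design does not secure.

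**Size of the possible bias.** The documents give no CGAS standard deviation and no rating difference. Both are assumptions here: SD = 10 points, δ from 0 to 5 points.

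| δ (points) | δ / SD | share of 0.50 |
|---|---|---|
| 0 | 0 | 0% |
| 1 | 0.1 | 20% |
| 3 | 0.3 | 60% |
| 5 | 0.5 | 100% |

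The table only converts an assumption into SD units. The sign of δ is equally unknown.

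**How often the T0 rater is the later one.** If an arm-specific therapist is named before 1:1 allocation and scores T0, that therapist's arm is the allocated one in about 50% of cases, so at most about 70 of 140 match. If the T0 rater is any one of the roughly 70 / 14 = 5 therapists at an institution, about 1 in 5 match, or 28 of 140. Therapists who deliver both treatments would raise these figures.

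**Cost of a change of rater.** Assume a baseline–outcome correlation of 0.5 with one rater, multiplied by 0.70 to 0.85 when the rater changes. Residual variance is proportional to 1 − r²: 1 − 0.5² = 0.75 with one rater; 1 − 0.425² = 0.819 and 1 − 0.35² = 0.878 with two. The increase is 0.819/0.75 = 1.09 to 0.878/0.75 = 1.17, that is 9% to 17%, if the rater changed for every youth. This is a loss of precision. Randomisation balances T0 ratings made before allocation, so it adds no bias.

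**The case against.** The case on the other side is substantial, and part of it stands.

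- *A reader might infer that the baseline rater cannot be the treating therapist.* The article does not say which therapist scores T0, and it says most therapists, not all, are tied to one arm. A match in up to about half of cases is possible. What can be said is that the T0 rater is unidentified and will often differ.
- *A reader might infer that the baseline itself is biased, or is scored with knowledge of the arm.* A different rater before allocation is harmless to validity. Scoring T0 after allocation would depart from the stated order of events and is not a feature of the plan.
- *A reader might infer that TAU therapists have no comparable preparation.* The article is silent on their training and supervision, and silence does not establish a difference.
- *A reader might take 0.3 to 0.5 SD as the expected bias.* Those values follow wholly from the assumed SD and shift, and zero is also possible.
- *Individual leniency averages out over some 35 therapists per arm.* This is correct. Only a shift common to an arm matters, and the documents give neither its size nor its direction.
- *The CGAS is described as reliable between raters.* That speaks to agreement among raters in general. It does not rule out a shift linked to knowing, and having delivered, the treatment.
- *Who fills in a form is a detail for the full protocol.* The missing name of the T0 rater would not be a finding on its own. The choice of therapists as raters, however, is stated in the article.
- *The self-rated ORS covers the same domain at all six assessments.* This limits the harm, but it does not supply the therapist perspective that the plan relies on.
- *Research assistants are not described as masked either.* This stands and limits what the fix can promise.

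**Conclusion.** The concern holds in a limited form. The T4 CGAS contrast is open to a rating difference between arms that the planned model cannot separate from the treatment effect. It rests on one inference, that later ratings come from the participant's own treating therapist. That is the natural reading of the article but is not stated outright.

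The magnitude is unknown: 0 to 0.5 SD under an assumed SD of 10 points and an assumed shift of 0 to 5 points. The often different rater at T0 is a matter of precision only.

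The consequence is confined to one secondary outcome. The primary outcomes and the sample size are untouched. The change is worth making because it is cheap and because this outcome alone carries the therapist's view of functioning.

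Separately, the text and Table 1 disagree on whether the CGAS is scored at T5, and the effectiveness analysis covers T5.

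**What to change.** 1. Have the research assistant who conducts the SCID-5-Junior at T0, T4 and T5 score the CGAS directly after the interview, and use that rating for the between-arm CGAS comparison. Assistants are not described as tied to an arm and are not judging their own treatment.
2. Do not tell the assistant the allocation where feasible, and state whether the rating is masked. Assistants work at the institutions and track assessments whose session counts differ for bi-weekly TAU, so masking may be incomplete. The change reduces rater bias but is not shown to remove it.
3. Keep the therapist ratings, including T2 where there is no interview, as a supportive informant measure labelled as unmasked. State which therapist scores each time point.
4. Reconcile the Secondary outcomes text with Table 1 on the CGAS at T5.

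The cost is one single-item rating added to an interview that already takes place, and a short CGAS module in the existing training. The training matters because the article describes the scale as one for mental health care workers, while the assistants include master students. The main downside is that an assistant sees the youth for less time than the therapist does.
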